### Effectiveness and efficiency outcome measures and assessments

The RESTORE-LIFE study will conduct a series of assessments designed to measure the response rate, durability of response to VNS Therapy in DTD, and overall long-term disease management of these patients based on changes in mood, severity of depression, mania, quality of life, psychosocial impairment, cognition, anxiety, suicidality, adjunctive antidepressant treatment usage, and safety assessments. The assessments will be conducted at regular time intervals during standard medical care as specified in the Schedule of Assessments (Table 1) to evaluate changes in clinical symptoms over time in response to adjunctive VNS Therapy. The primary, secondary, and exploratory outcome measures along with information on the related scales and questionnaires are listed in Table 2.

**Table 2 Tab2:** List of effectiveness and efficiency outcome measures

Outcome measures	Measurement details with clinician-rated and patient-reported scales
**Primary outcome measure**	
Rate of response	Decrease of ≥50% in MADRS total score from baseline to 12 months post-implant. The MADRS is a physician-rated instrument to assess the severity of depressive symptoms during the past week [39, 40].
**Secondary outcome measures**	
Duration of response	The difference between the first recorded date of post-baseline MADRS score when response is achieved (based on a decrease in baseline MADRS score of ≥50%) and the first date at which the MADRS score reaches a level of < 40% from baseline.
Duration of response	Change in MADRS score over time
Duration of response	Cumulative percentage of first-time responders (based on reduction in baseline MADRS score of ≥50%) and cumulative remission (based on MADRS score of ≤9 at any post-baseline visit) over time.
Changes in mood, depression, and mania scores	This will be based on changes in MADRS, QIDS-SR, and ASRM. The QIDS-SR questionnaire measures symptoms of mood and depression [41]. The ASRM measures the presence and severity of manic and hypomanic symptoms, specifically in patients diagnosed with bipolar disorder [42]. Note: ASRM is an optional assessment.
Changes in quality of life and psychosocial impairment	The WPAI:D questionnaire measures impairments in work and activities in depression [43]. The Q-LES-Q-SF scale measures the degree of enjoyment and satisfaction experienced during the past week [44]. The EQ-5D-5L questionnaire measures generic health status and quality of life [45].
Changes in suicidality	Based on Item Number 10 of MADRS and Item Number 12 of QIDS-SR.
Changes in antidepressant treatments	This will include data on drug dosage and type of antidepressant medications, and duration and intervals of maintenance ECT, rTMS, and/or psychotherapy.
Changes in cognition	THINC-it® Tool includes the 5-item PDQ-5, in addition to 4 traditional cognitive assessments which have been reconfigured for computer-based administration. Thus, it assesses both a patient’s subjective assessment as well as key objective measures of cognitive function [46]. Note: THINC-it is an optional assessment.
Changes in anxiety	The GAD-7 measures severity of generalized anxiety disorder [47]. Note: GAD-7 is an optional assessment.

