### Sample size and statistical analysis considerations

As this is an observational study designed to describe the characteristics of VNS Therapy in a real-world setting, the statistical analysis of the study outcomes will focus on a combination of descriptive and exploratory statistics, rather than confirmation of formal hypothesis testing; that is, the provision of two-sided 95% confidence intervals rather than *p*-values. As an additional consequence, the emphasis provided in the study will be on the precision of the estimate. A sample size of 500 patients is sufficient to provide higher precision of the estimates in term of width of the 95% confidence interval for the key study endpoints:
For the primary endpoint based on MADRS, the width of the 95% CI will be of 7.8% assuming an observed response of approximately 25%.For the secondary endpoint based on Q-LES-Q-SF response (and the available Q-LES-Q-SF data obtained in the D-23 study), the width of the 95% CI will be 8.9% assuming an observed response of approximately 50% [49].

Enrolled analysis population will include all participants who signed the informed consent and who satisfy the study eligibility criteria. Safety analysis population will include all enrolled participants who were implanted with the VNS Therapy system and received at least one dose of stimulation. The full analysis set population will include all participants in the safety analysis population with evaluable baseline device data; that is, patients who have the device implanted and received at least one dose of stimulation. As such, for this study, the full analysis set population is equivalent to the safety analysis population.

The full analysis set population will be used mainly for all effectiveness and efficiency summaries and is considered the primary population. Descriptive statistics will be calculated using as reference the number of participants in the relevant analysis population, according to the nature of the data (i.e., continuous, discrete, time to event) as follows: continuous variables by number of non-missing observations, arithmetic mean, standard deviation, minimum and maximum values, median and quartiles and categorical variables by absolute and relative frequencies.

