#### Primary analysis

The primary endpoint of response ─ defined as a decrease in MADRS total score of at least 50% from baseline to 12 months post-implant ─ will be provided for patients who were experiencing a major depressive episode at the time of enrolment (i.e. a baseline MADRS total score ≥ 20). The number and percentage of participants with response and the associated 95% confidence interval will be presented.

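### Cumulative first response and first remission are filed under duration of response, but they count first attainment and cannot show whether benefit lasts

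*Protocol article*

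**What the plan says.** Table 2 of the protocol article (Secondary outcome measures) has three entries labelled as duration of response.

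1. A direct duration: "The difference between the first recorded date of post-baseline MADRS score when response is achieved" (a fall of at least 50%) and "the first date at which the MADRS score reaches a level of < 40% from baseline".
2. "Change in MADRS score over time".
3. "Cumulative percentage of first-time responders (based on reduction in baseline MADRS score of ≥50"%), together with "cumulative remission (based on MADRS score of ≤9 at any post-baseline visit) over time".

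The third entry has no confirmation or persistence rule.

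The baseline floor is written for the primary endpoint, in Study design and again in Primary analysis, where the response rate "will be provided for patients who were experiencing a major depressive episode at the time of enrolment (i.e. a baseline MADRS total score ≥ 20"). Under Sample size and statistical analysis considerations, "The full analysis set population will be used mainly for all effectiveness and efficiency summaries". That set is defined by implantation and at least one dose of stimulation, with no MADRS threshold. The eligibility section sets no MADRS minimum either, although the MINI must confirm a mood disorder in the depressed phase.

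**The concern.** Durability of response is a stated aim of the study (Study aims; Effectiveness and efficiency outcome measures). A patient who meets the response criterion once and relapses at the next visit stays in the cumulative count for good. The count therefore says when patients first got better, not whether they stayed better. MADRS is scheduled at nine visits up to month 36 and then every six months to month 60, so a patient has up to 13 chances to qualify, and fluctuation in scores alone will lift the curve. With no control group, nothing in the design separates that accumulation from treatment benefit. Under its present label, a curve that climbs for years could be taken as growing, lasting benefit even if the share of patients well at each visit were constant.

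A separate and smaller matter is the population. Remission is an absolute cut-off, and a patient with a low baseline can reach it with little change. The restriction that prevents this is written only for the primary endpoint.

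**Working it through.** **The plan's own figure.** The article gives no figure for the cumulative outcomes. Its only related numbers are the widths of the 95% confidence intervals at n = 500. The exact (Clopper–Pearson) interval gives 7.77% at 125/500 (stated 7.8%) and 8.94% at 250/500 (stated 8.9%). Both reproduce, and neither bears on this point.

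**Inputs for the illustration**
- Response rate 25%: the article's planning value for month 12. Holding it flat at every visit is my assumption.
- Visits (Table 1): months 3, 6, 9, 12, 15, 18, 24, 30, 36, then 42, 48, 54, 60. That is 4 visits by month 12, 9 by month 36 and 13 by month 60. Months 12 to 36 contain 6 visits (12, 15, 18, 24, 30, 36).
- Between-visit correlation ρ of 0.6 to 0.95 on a latent normal scale, equal for all pairs of visits, and no attrition: assumptions. The article gives neither a correlation nor a dropout rate.

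**Formulas.** Given a patient effect u ~ N(0,1), the probability of response at any one visit is

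p(u) = Φ[(√ρ·u − 0.674)/√(1−ρ)], where 0.674 is the 75th percentile of N(0,1).

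- Cumulative response after k visits = 1 − E[(1 − p(u))^k]
- Response at all six visits, months 12 to 36 = E[p(u)^6]

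Numerical integration gives:

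| ρ | At each visit | Cumulative, month 12 (k=4) | Cumulative, month 36 (k=9) | Cumulative, month 60 (k=13) | Held at all six visits, months 12–36 |
|---|---|---|---|---|---|
| 0.60 | 25% | 48.7% | 61.9% | 67.1% | 4.5% |
| 0.70 | 25% | 45.1% | 56.0% | 60.5% | 6.5% |
| 0.80 | 25% | 41.0% | 49.5% | 53.0% | 9.3% |
| 0.90 | 25% | 36.0% | 41.6% | 43.9% | 13.4% |
| 0.95 | 25% | 32.6% | 36.4% | 37.9% | 16.6% |

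The true rate never moves, yet the cumulative figure rises throughout. At month 36 it is 36.4/16.6 = 2.2 times the sustained rate at ρ = 0.95 and 61.9/4.5 = about 14 times at ρ = 0.6. Compared with the per-visit rate, the ratio is 1.3 to 1.9 at month 12 (32.6/25 to 48.7/25) and 1.5 to 2.5 at month 36 (36.4/25 to 61.9/25).

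**Baseline floor.** The fall needed to reach MADRS 9 is baseline − 9:

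| Baseline | Points needed | Share of baseline |
|---|---|---|
| 9 or less | 0 | 0% |
| 10 | 1 | 10% |
| 12 | 3 | 25% |
| 15 | 6 | 40% |
| 20 | 11 | 55% |

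Below a baseline of 18, remission needs a smaller fall than response does (baseline − 9 is less than baseline/2).

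The effect on the overall figure depends on how many patients enter below 20, which the article does not say. Suppose 30% of patients at 20 or above ever remit, a share s of the set enters below 20, and a fraction q of those ever remit. The overall figure is (1 − s)·30% + s·q.
- s = 2%, q = 40%: 29.4% + 0.8% = 30.2%
- s = 10%, q = 100%: 27.0% + 10.0% = 37.0%

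All three inputs are assumed. The effect is small unless many patients enter below the floor.

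**The case against.** The strongest reply is that the article does not rest durability on the cumulative measures. The first entry under the same label ends at loss of response, taking its end rule to mean that the reduction has shrunk below 40%, so it registers relapse. The second follows MADRS over time, and the secondary analyses add scores and changes from baseline at each follow-up with confidence intervals. A flat or worsening mean would appear beside a rising curve. The cumulative entries also say openly that they are cumulative and first-time, and they have a proper use, because the background stresses delayed onset. The analysis is descriptive, and no decision hangs on these figures. All of this stands. It rules out the inference that the study will overstate sustained benefit, or that it has no other durability outcome.

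It does not settle the point. The direct duration exists only for patients who respond, and the mean score is not a response rate. Neither gives the share of implanted patients who are well at month 24 or 36, or who stayed well until then. The visit-by-visit summaries are promised for continuous secondary endpoints.

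The illustration has real limits. The correlations are assumed, a flat 25% from month 3 ignores gradual onset, attrition is left out, remission is not modelled, and 13 visits is a maximum because the study may stop once the last participant reaches month 36. A reader might infer that the cumulative figure is at least double the true rate. That depends on the correlation, and the figure stays below double at month 12 throughout the range used.

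On the baseline floor, the article does not say that secondary outcomes omit it. That is inferred from where the restriction is written, and the unseen analysis plan may settle it. Requiring a current depressive phase also makes very low baselines unlikely.

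**Conclusion.** The point holds in a limited form. Cumulative first response and first remission are misfiled as duration measures. They record first attainment, ignore relapse, and overstate sustained benefit if read as durability, which their label invites. The other entries under that label do address durability, but no per-visit response or remission rate after month 12 and no sustained-response rate is named.

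Under the stated assumptions, a flat 25% response rate yields cumulative response of 33–49% at month 12 and 36–62% at month 36, against 4.5–17% held at all six visits from month 12 to month 36. The direction follows from the definition, whereas the size follows from the assumed correlations.

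A reader might also infer that the curve can only rise because the baseline floor is missing. The rise comes from cumulation alone, and only on a fixed denominator or in a time-to-event estimate; a percentage of patients still in follow-up could fall. The floor is a separate, smaller issue that bears mainly on remission.

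The primary 12-month response rate is a point-in-time measure and is unaffected. This is worth correcting, but it does not threaten the main result.

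**What to change.** 1. Present the cumulative measures as time to, or cumulative incidence of, first response and first remission, and take them out of the duration heading.
2. For durability, add the percentage in response and in remission at each visit on a fixed denominator. Also add sustained response from month 12 to month 24 and from month 12 to month 36. Do not count missed visits or dropout as sustained, and vary that rule in a sensitivity analysis. If only attended visits counted, a month-12 responder who then left would pass as sustained.
3. Apply the baseline MADRS restriction of 20 or more to the secondary response and remission summaries, and say so.

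The MADRS data are already scheduled, so no new collection is needed. The cost is a change of wording in the outcome table and analysis plan, a little more analysis work, and less favourable secondary percentages.

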**Exploratory outcome measures**	
Changes in positive affect, negative affect, hedonic tone, cognitive functioning, overall functioning, meaningfulness of life, and happiness with adjunctive VNS treatment	The LAPS questionnaire assesses negative affect, positive affect, hedonic tone, and meaningfulness of life [48].
Healthcare resource utilization analysis	Healthcare utilization data will be used to assess the main sources of resource utilization associated with DTD management per patient who have been subsequently treated with VNS Therapy. The collected data will include the number of depression-related emergency room visits leading to hospitalizations, antidepressant medication usage, and adjunctive antidepressant treatments before and after the start of VNS Therapy.

The patient-completed self-report assessments will be completed by participants who are able to complete the assessments with minimal assistance

The ASRM, THINC-it Tool, and GAD-7 are optional assessments that will be completed at selected and interested sites only, and participants will be selected to complete the assessments based on the study physician’s clinical judgment

Note that only validated scales and questionnaires are being used in this study. For each participating country, the sponsor obtains fully licensed and validated translations of the scales and questionnaires in the local languages.

Some of these scales and questionnaires will be completed by the study participants, and the other scales will be completed and assessed by the study investigator/physician or qualified mental health care professional with the training and clinical experience necessary to conduct these assessments. Care will be taken to ensure that the assessments are conducted in a similar manner and condition at all visits for a given participant.

### Healthcare resource utilization

An exploratory analysis will be conducted with the aim of identifying the main sources of resource utilization related to patients with DTD who are subsequently treated with VNS Therapy (Table 2). This exploratory analysis is not being planned to demonstrate any resource consumption savings associated with VNS therapy as the study is not designed for this purpose.

To enable a calculation of the expenditures associated with the use of the VNS Therapy system, the following data will be collected (prior to enrolment and during study): number of emergency room visits (depression related or not); number of depression related emergency room visits leading to hospitalization; number, dosage, and type of antidepressant medications and psychotropics; number of adjunctive antidepressant treatments such as ECT, rTMS, and/or psychotherapy (such as interpersonal therapy and cognitive behavioural therapy). The data will be obtained from patient’s self-reports and/or medical records, as available.

For those patients who provide consent to collect additional data and who are enrolled in a country with a national healthcare database, a more detailed resources consumption analysis will be conducted (such as number of depression related general practitioner, emergency room visits and/or outpatient visits).

### Safety assessments

All participants will be monitored for safety and evaluated for any depressive symptoms (including suicidal ideation) by completing study assessments throughout the study. Additionally, the participants will be instructed to contact their physician in case of worsening depression/suicidality. The sponsor is responsible for the ongoing safety evaluation of the VNS Therapy system, review of reported adverse events, investigation of unanticipated serious adverse device effects, and notification of regulatory authorities per applicable requirements.

For safety evaluation, data will be collected on adverse events, serious adverse events, VNS Therapy related adverse events and serious adverse events (including the use of the device), unanticipated adverse device effects, and device deficiencies. Adverse events will be followed until (a) resolution, (b) stabilization, (c) the end of the study, or (d) if a study physician and/or sponsor determines that a device-related adverse event must be followed until its conclusion which extends beyond the end of the study.

The study physicians should reference the VNS Therapy Physician’s Manual for a list of anticipated adverse events that have been frequently reported in clinical studies. Any serious adverse device effect not listed in the Physician’s Manual will be considered as unanticipated.

### Concomitant treatments

During participation in the study, participants will not be required to stop or change any concomitant medications or treatments. All adjunctive treatments for the treatment of depression are allowed per physician’s clinical judgment based on site’s standard of care.

Participants enrolled in this study must be receiving at least one antidepressant treatment (ie, antidepressant drug, maintenance ECT, or formal psychotherapy including supportive psychotherapy) or mood-stabilizing treatment for bipolar patients (such as lithium, anticonvulsants, or atypical antipsychotics). Concomitant use of antidepressant medications and psychotropics, non-pharmacologic antidepressant treatments for depression, and inpatient hospitalizations will be recorded.

### Sample size and statistical analysis considerations

As this is an observational study designed to describe the characteristics of VNS Therapy in a real-world setting, the statistical analysis of the study outcomes will focus on a combination of descriptive and exploratory statistics, rather than confirmation of formal hypothesis testing; that is, the provision of two-sided 95% confidence intervals rather than *p*-values. As an additional consequence, the emphasis provided in the study will be on the precision of the estimate. A sample size of 500 patients is sufficient to provide higher precision of the estimates in term of width of the 95% confidence interval for the key study endpoints:
For the primary endpoint based on MADRS, the width of the 95% CI will be of 7.8% assuming an observed response of approximately 25%.For the secondary endpoint based on Q-LES-Q-SF response (and the available Q-LES-Q-SF data obtained in the D-23 study), the width of the 95% CI will be 8.9% assuming an observed response of approximately 50% [49].

Enrolled analysis population will include all participants who signed the informed consent and who satisfy the study eligibility criteria. Safety analysis population will include all enrolled participants who were implanted with the VNS Therapy system and received at least one dose of stimulation. The full analysis set population will include all participants in the safety analysis population with evaluable baseline device data; that is, patients who have the device implanted and received at least one dose of stimulation. As such, for this study, the full analysis set population is equivalent to the safety analysis population.

The full analysis set population will be used mainly for all effectiveness and efficiency summaries and is considered the primary population. Descriptive statistics will be calculated using as reference the number of participants in the relevant analysis population, according to the nature of the data (i.e., continuous, discrete, time to event) as follows: continuous variables by number of non-missing observations, arithmetic mean, standard deviation, minimum and maximum values, median and quartiles and categorical variables by absolute and relative frequencies.

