Antidepressant treatments ^d^	X			X	X
Adverse events monitoring	X	X	X	X	X
Study completion/termination record ^e^			At study exit		

^a^ QIDS-SR, Q-LES-Q-SF, EQ-5D-5L, THINC-it, GAD-7, and Health Care Utilization Form are not collected at 3, 9, and 15 months

^b^The ASRM, THINC-it, and GAD-7 are optional assessments to be completed at selected sites only and will be upto the investigators’ clinical judgment to decide which participants complete the assessments

^c^Health care utilization data (eg, number of depression-related emergency room visits and/or hospitalizations) will be obtained where possible (patient reported and/or based on medical records, whichever is available). More detailed information may be derived from a national health care database, if available, and if the patient provides consent to collect this data

^d^ Antidepressant medications and psychotropics, ECT, rTMS, and/or psychotherapy (such as interpersonal therapy and cognitive behavioural therapy)

^e^ Including participant satisfaction record (if applicable)

All participants will exit the study after completing 60 months of post-implantation follow-up, or at study end (whichever comes first). The study may be stopped when the last participant has reached the 36 months of follow-up. Study end will be communicated to all participating sites. The study will be considered completed when all enrolled participants complete the study completion/termination record.

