### Intervention (VNS therapy implant procedure and programming)

Per standard of care, all participants will be implanted with a commercially available implantable VNS Therapy System (manufactured by LivaNova) with generator, lead, and external programming system. The VNS Therapy Physician’s Manual and the Implant Manual contain instructions regarding the implantation procedure and initial device parameters/diagnostics. Surgeons performing the implantation procedures should have the appropriate qualifications and training to perform the surgery. VNS Therapy consists of a pulse generator which is surgically implanted subcutaneously in the thoracic area (usually the left side) and delivers intermittent electrical signals to the vagus nerve via a lead that is partially wrapped around the vagus nerve in the mid-cervical region. The electrical signals are relayed to various regions of the brain. The system is programmed via an external programming device (see Fig. 1).

Following device implantation, the device must be switched ON and titrated to clinical efficacy as per standard medical care. Clinicians program the system using an external programming device and rely on attentive patient-specific titration to select the right combination of adjustable parameters (output current, frequency, pulse width, and signal ON and OFF times) to attain full activation of the vagus nerve while minimizing stimulation-induced side effects. Usually stimulation is delivered intermittently, typically 30 s ON, 5 min OFF. The rate of titration varies by patient and their response until a therapeutic dose has been established; all sites are encouraged to reach a stimulation of minimally 1 mA (considered minimal therapeutic dose) at a duty cycle of minimally 10%. This recommendation is based on previous findings that a higher delivered charge predicted greater sustained antidepressant effects [38].

The sponsor has developed detailed metrics on the titration procedure to assist clinicians reach the optimal therapeutic dose of VNS for individual patients. Patients who are under-dosed and do not achieve the therapeutic dose of VNS will be identified via a so-called ‘risk-based study monitoring’ method. The sponsor will contact sites that have patients below therapeutic dose and if needed the sponsor will provide technical support to the principal investigators on titrating VNS parameters to reach the minimal therapeutic dose as reasonably possible.

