#### Study participants

Participant disposition including the number of participants enrolled/implanted and the numbers completing or discontinuing (including the reason for discontinuation) will be provided. Information on demographics, implant characteristics, medical history, medications, and treatments will be summarized as appropriate.

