#### Safety analysis

Safety data will be summarized descriptively, based on the safety analysis population (defined above). Adverse event data will be summarized by means of number of participants with at least one event, incidence rates, crude incidence rates. Similarly, statistics for serious adverse event; adverse device effect; serious adverse device effect; unanticipated serious adverse device effect and deaths will be presented.

Note that an adverse event with a ‘related’ causal relationship to the VNS therapy will be considered an Adverse Device Effect. Details of any recorded device deficiencies will be listed. Further safety tabulations may be presented, as appropriate.

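### The safety population requires stimulation, so participants implanted (or with implantation attempted) but never stimulated fall out of the planned safety rates

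*Protocol article*

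**What the plan says.** The section on sample size and statistical analysis considerations sets out three nested populations.

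- Enrolled: "Enrolled analysis population will include all participants who signed the informed consent and who satisfy the study eligibility criteria".
- Safety: "Safety analysis population will include all enrolled participants who were implanted with the VNS Therapy system and received at least one dose of stimulation". Both conditions must be met, and the set is drawn from the enrolled.
- Full analysis set: described in the same terms, with the conclusion that "the full analysis set population is equivalent to the safety analysis population".

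The Safety analysis section then states: "Safety data will be summarized descriptively, based on the safety analysis population (defined above". It covers adverse events, serious adverse events, adverse device effects, serious and unanticipated device effects, and deaths. It names no other population.

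Three other places bear on the point. Table 1 marks the row "Adverse events monitoring" at every visit column, including baseline and implant (Day 0). The Intervention section describes surgical placement of a generator and a lead on the vagus nerve, and then a separate step: "Following device implantation, the device must be switched ON and titrated to clinical efficacy as per standard medical care". The Study participants section promises disposition: "Participant disposition including the number of participants enrolled/implanted and the numbers completing or discontinuing (including the reason for discontinuation) will be provided".

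**The concern.** A safety set should include everyone exposed to the risk being described. Here exposure begins with the operation, but membership of the set begins with the first dose of stimulation. The people between those two points are not a random sample of the implanted. Some of them may be there because of a surgical event serious enough that the device was never activated. For them, exclusion depends on the outcome being measured.

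Safety assessment is among the stated aims, and the Discussion expects the results to inform decisions about the therapy as an effective and safe option. What is at stake is the peri-operative part of that picture: rates of serious events, device effects and deaths would describe only participants who got as far as stimulation.

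**Working it through.** **Does the text exclude these participants?** Setting the definitions side by side:

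| Participant | Adverse events collected? | In the safety set? |
|---|---|---|
| Implanted and stimulated on schedule | Yes | Yes |
| Implanted, surgical event delays activation, stimulated later | Yes | Yes; earlier events are not discarded |
| Implanted, never stimulated | Yes | No |
| Implantation attempted and aborted | Yes | No |
| Implanted and stimulated, later found ineligible | Yes | No, if *enrolled* is read literally |

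The third and fourth rows are the defect. The fifth follows from nesting the safety set in the enrolled set.

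**How large could the effect be?** The article states no rate of non-activation or of surgical complications, so there is no figure of its own to reproduce on this point. A general expression still helps. Let *w* be the proportion never stimulated among all with implantation performed or attempted, *p_n* the event rate in that group, and *p_s* the event rate among the stimulated.

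- Rate in all: *w p_n* + (1 − *w*) *p_s*
- Rate in the planned safety set: *p_s*
- Shortfall: *w* (*p_n* − *p_s*)

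The planned rate is too low whenever events are more common among the never stimulated. The shortfall is zero if the two rates are equal, and can never exceed *w*.

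**A purely hypothetical illustration.** Assume 500 participants with implantation performed or attempted (the planned minimum number implanted is 500), 10 with the event among the stimulated (about 2%), and the extreme case in which every never-stimulated participant had the event (*p_n* = 1). Only the 500 comes from the article.

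| Never stimulated | Planned safety set | All performed or attempted | Shortfall (points) |
|---|---|---|---|
| 2 | 10/498 = 2.01% | 12/500 = 2.40% | 0.39 |
| 5 | 10/495 = 2.02% | 15/500 = 3.00% | 0.98 |
| 10 | 10/490 = 2.04% | 20/500 = 4.00% | 1.96 |
| 15 | 10/485 = 2.06% | 25/500 = 5.00% | 2.94 |

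If only 5 of 10 never-stimulated participants had the event, the comparison is 10/490 = 2.04% against 15/500 = 3.00%, a shortfall of 0.96 points. These rows show direction and upper bounds. They are not estimates for this study.

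**Does the change disturb anything else?** The article's precision figures for 500 patients reproduce with the exact (Clopper-Pearson) interval: 125/500 gives a width of 7.77% (stated 7.8%) and 250/500 gives 8.94% (stated 8.9%). Both concern effectiveness endpoints, so redefining the safety set leaves them unchanged.

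**The case against.** The best defence is that the gap is narrow. The device must be switched on after implantation, Table 1 already records parameter settings on the day of implant, and a single dose at any time is enough to qualify. A reader might infer that every infection, nerve injury or other complication before activation is lost. The documents do not support that: if activation is only delayed, the participant enters the set with the earlier events intact. This limit stands.

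Nor does anything disappear from the record. Events are collected, the sponsor reviews reported adverse events and notifies authorities, disposition shows the numbers implanted and the reasons for discontinuation, device deficiencies are listed, and further safety tabulations are allowed. That is also true, but none of it commits the study to adverse event rates in all implanted participants. Disposition gives counts and reasons, and the further tabulations are optional with no population named.

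A third objection is that the study is single-arm and descriptive with an effectiveness primary endpoint, so the safety wording does not undermine its main result. That is right, and it limits how much weight the point should carry. Requiring stimulation for the effectiveness set is a conventional choice and is not disputed here.

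It cannot be said that the definition is merely left to an unseen analysis plan. The article fixes it explicitly.

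**Conclusion.** The definition is wrong as written for an implanted device. Participants with implantation performed or attempted who never receive stimulation fall outside every planned safety rate, and for some of them the reason may be the very event that the rates are meant to count. The bias runs downward if events are more common in that group, which is plausible but is an assumption. Its size cannot be derived from the article and may be small; it is bounded by the proportion never stimulated.

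Two stronger readings should be resisted. One is that complication rates will be materially under-reported: no figure in the article supports that, and the percentages above rest on assumed inputs. The other is that the eligibility condition is a second outcome-dependent exclusion. Literally, it does remove implanted participants later found ineligible, and eligibility should not filter safety data. But eligibility is assessed at baseline against criteria that the article calls minimal, and nothing shows that such removals relate to outcome. This part is secondary.

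The point should be fixed, but the primary result does not depend on it.

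**What to change.** Make three wording changes to the analysis populations:

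1. Define the safety population as all consented participants in whom implantation was performed or attempted, regardless of whether stimulation was delivered and regardless of later eligibility findings.
2. Keep the condition of at least one dose of stimulation for the full analysis set only.
3. Delete the statement that the full analysis set and the safety population are equivalent.

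The cost is a text amendment in the protocol and in any analysis plan that repeats the definition. Table 1 already schedules adverse event collection from baseline and at implant, so no new data collection is needed. Reported complication rates may become slightly less favourable.
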